#### Secondary outcomes

Analyses of secondary outcomes will be competed in the mITT population. The size of the treatment effect will be the difference in outcome data (BMI, questionnaires, neurocognitive outcomes) between the active and sham treatment arms for both tDCS and rTMS, respectively, at 4 weeks, 8 weeks, and 20 weeks post treatment. These effect sizes will control for pre-treatment scores. Descriptive statistics will be used to show remission rates for all treatment arms at post 8 weeks and 20 weeks post treatment. Generalised linear mixed models will be used to compare the treatment arms for mood and psychological symptom outcomes. Exploratory analyses will investigate associations between changes in mood and neurocognition with active tDCS and rTMS, and improvement in core eating disorder symptoms.

Generalised linear models will be used to compare cost and quality of life/utility values (from AQoL-4D) between treatments arms over the 8 week randomised treatment. Cost effectiveness analysis will compare the health outcomes and economic outcomes (costs of duration of inpatient stay and readmissions during the follow up period) associated with both treatment modalities.

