## Methods

### Design

This double-blind, randomised, sham-controlled trial will compare rTMS and tDCS acceptability and clinical outcomes in patients with AN. This study protocol was prepared in accordance with the SPIRIT and CONSORT guidelines. Participants will be randomised to one of four groups (2:1:2:1 ratio): active or sham tDCS, or active or sham rTMS. The brain stimulation protocols involve 84 sessions of tDCS (active or sham) or 56 sessions of rTMS (active or sham) over an 8 week treatment period. Participants in all groups will also receive treatment as usual (TAU) across the study duration. Following the end of 8 week randomised controlled period assessment, participants in all groups will have the option of receiving an additional open label 12 weeks of at-home, remotely supervised tDCS. A follow up assessment will be conducted at 20 weeks post treatment. A flowchart of the study is shown in Fig. 1.

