### Optional open label active tDCS treatment

Following the end of 8 week randomised controlled period assessment, participants in all groups will have the option of receiving an additional 12 weeks of daily (1 session per day), at-home, remotely supervised active tDCS, until end week 20.

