### Outcome measures

Outcome measures and administration timepoints are presented in Table 1.

**Table 1 Tab1:** Outcome measures of the RCT

Measure	Mode	Baseline	Weeks 1–3	Week 4	Week 8	Weeks 10, 12, 14, 16, 18	Week 20
Core an symptoms							
Eating Disorder Examination Questionnaire, EDE-Q, *total score, subscales scores* [30]	Electronic	✓		✓	✓	✓	✓
**Weight—**BMI, *kg/m*^*2*^		✓		✓	✓		✓
Mood							
Montgomery Asberg Depression Rating Score, MADRS, *total score* [64]	Electronic	✓	✓	✓	✓		✓
Neurocognition							
**Perseveration** Wisconsin Card Sorting Test, WSCT, *numbers of errors* [33]	Computer	✓			✓		✓
**Response inhibition** STROOP Colour Word Test, *response time in milliseconds* [70]	Computer	✓			✓		✓
**Field dependence vs independence** Group Embedded Figures Test, GEFT, *completion time in seconds, total number of correct forms* [75]	Paper	✓			✓		✓
**Attention and cognitive flexibility** Trail Making Test parts A & B, TMT, *completion time in seconds* [66]	Paper	✓			✓		✓
Psychological symptoms							
Depression Anxiety and Stress Scale, DASS-21, *subscales total scores* [54]	Electronic	✓	✓	✓	+ Weeks 5–7✓	✓	✓
Quality of life							
The Assessment of Quality of Life Instrument, AQoL-4D, *total score* [38]	Electronic	✓			✓		✓
Interpersonal relations							
Circumplex Scales of Interpersonal Efficacy, CSIE-32, *subscales total scores* [52]	Electronic	✓			✓		✓
**Experience of treatment** OPTIONAL Semi-structured interview	Zoom				✓		✓
**Assessment of blinding**	Electronic				✓		
Economic outcomes							
Administration cost	Hospital data		✓	✓	✓	✓	✓
Medications			✓		✓		✓
Psychology sessions							✓
Length of stay				✓	✓		
Readmissions							✓

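### The week-20 secondary contrast is defined as active versus sham, although every arm may by then have had 12 weeks of open-label active tDCS, and the visit is mislabelled as 20 weeks post treatment

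*Protocol article*

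**What the plan says.** The Analysis section, under Secondary outcomes, defines one treatment effect for BMI, the questionnaires and the neurocognitive tests. It is the difference "between the active and sham treatment arms for both tDCS and rTMS, respectively, at 4 weeks, 8 weeks, and 20 weeks post treatment". The only adjustment named is for baseline: "These effect sizes will control for pre-treatment scores".

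The Design section sets the randomised phase at "84 sessions of tDCS (active or sham) or 56 sessions of rTMS (active or sham) over an 8 week treatment period". The section on optional open-label treatment then states that "participants in all groups will have the option of receiving an additional 12 weeks of daily (1 session per day" and that this is "at-home, remotely supervised active tDCS, until end week 20". The Discussion confirms that the offer goes to everyone who completes the first 8 weeks, whatever their arm.

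On the timing of the last visit, the Design section says "A follow up assessment will be conducted at 20 weeks post treatment", and the Abstract uses the same label. For the schedule itself the article refers to a table: "Outcome measures and administration timepoints are presented in Table 1". The last column of Table 1 is week 20. The Optional interview section also places the second interview at a week-20 follow-up.

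**The concern.** One definition of the effect is applied at three times, but the comparison has a sham control at only two of them. At weeks 4 and 8 the arms differ by randomised stimulation, active or sham. At week 20 any participant in any arm may have spent the preceding 12 weeks on active tDCS. In the tDCS pair the comparison becomes early tDCS against optional delayed tDCS. In the rTMS pair it becomes rTMS then optional tDCS against sham then optional tDCS, so a second modality enters.

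The label adds to this. Someone reading a result described as 20 weeks post treatment would picture participants long off stimulation. By the article's own schedule the visit coincides with the end of a stimulation phase.

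What is at stake is the interpretation of the longest-term arm comparison. The primary efficacy analysis is the pre-to-post change within the active arms, so the secondary section is where the article specifies its active-versus-sham effects. One of the three time points there does not carry the meaning given to it.

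**Working it through.** **Inputs, all from the protocol article**
- Randomised, sham-controlled period: 8 weeks (Design; Discussion).
- Open-label active tDCS: 12 weeks, one session per day, optional, all arms, ending at week 20 (Optional open label active tDCS treatment).
- Randomised tDCS: twice daily for 4 weeks, then daily for 4 weeks. Randomised rTMS: twice per weekday for 4 weeks, then twice a day on 2 days a week for 4 weeks (Interventions).
- Visits: baseline, weeks 1–3, 4, 8, 10 to 18 in steps of two, and 20, with some measures also at weeks 5–7 (Table 1).
- Open-label uptake: not given.

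**Step 1: reproduce the stated session counts**
- tDCS: 2 × 7 × 4 + 1 × 7 × 4 = 56 + 28 = 84, as stated.
- rTMS: 2 × 5 × 4 + 2 × 2 × 4 = 40 + 16 = 56, as stated.

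**Step 2: place the last visit**
- End of open label: 8 + 12 = week 20, which agrees with the stated end.
- Time since the end of randomised treatment: 20 − 8 = 12 weeks.
- Time since the end of open-label treatment: 20 − 20 = 0 weeks.
- A visit truly 20 weeks after treatment would fall at 8 + 20 = week 28, counted from the end of randomised treatment, or at 20 + 20 = week 40, counted from the end of open label. Table 1 has neither. The label is off by 8 weeks on the first count and by 20 weeks on the second.

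**Step 3: possible exposure by week 20**
- A sham participant who accepts and adheres: 12 × 7 = 84 active tDCS sessions, equal to the full randomised active tDCS course.
- An active-tDCS participant who does so: 84 + 84 = 168 active tDCS sessions.
- An active-rTMS participant who does so: 56 rTMS sessions plus 84 tDCS sessions.

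These are maxima, because the phase is optional.

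**Step 4: what each time point estimates**

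| Time | Sham control in place? | What the difference between arms compares |
|---|---|---|
| Week 4 | Yes | Active versus sham |
| Week 8 | Yes | Active versus sham |
| Week 20 | No | Active-first versus sham-first, each followed by optional active tDCS |

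Adjusting for pre-treatment scores does not change the last row, because the open-label exposure arises after week 8.

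**Step 5: can the distortion be sized?** No. If sham participants take up tDCS and benefit while the active arms gain nothing more, the week-20 difference shrinks. If the active arms take it up more often or gain further from it, the difference can widen. The article gives no uptake by arm, so neither size nor sign follows from it.

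**Step 6: week 4 against Table 1.** The same sentence asks for week-4 effects on all outcomes. Table 1 collects the EDE-Q, BMI, MADRS and DASS-21 at week 4. It does not collect the neurocognitive tests, AQoL-4D or CSIE-32 then, so their only sham-controlled post-baseline visit is week 8.

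**The case against.** The strongest reply is that comparing randomised arms at week 20 is legitimate: it is a treatment-policy comparison of two sequences and keeps the protection of randomisation. That is correct. The fault is not that the comparison exists, but that the article gives it the same name and definition as the sham-controlled comparisons at weeks 4 and 8.

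A second reply is that the label is loose wording. The open-label section, Table 1 and the interview section all fix the visit at week 20, and the 4 and 8 weeks in the same sentence are plainly counted from treatment start. Data collection is therefore not at risk. This also stands, but reading the label that way places the contrast exactly at the end of open-label active tDCS, so the definition of the effect still needs correcting.

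A third reply is that these are secondary outcomes in a self-described pilot, and that the article limits its sham-controlled period to 8 weeks in the Discussion and its cost and utility models to the randomised period. This is right, and it limits the weight of the point.

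A reader might infer more than the text supports:
- **Remission and readmissions.** It is tempting to say that these active-versus-sham comparisons fail too. Remission is reported only descriptively by arm, and readmission costs belong to a comparison of modalities, so neither is specified as an active-versus-sham effect.
- **Mixed models for mood and psychological symptoms.** It is tempting to say that they run past week 8. The article states no time window for them, and that detail may sit in a document not shown.
- **A claim of lasting benefit.** The article does not promise sham-controlled durability at week 20. It links longer-term benefit to the continuation tDCS option.

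**Conclusion.** The point holds for the secondary outcomes and should be fixed. After week 8 there is no sham control, so the week-20 difference is a comparison of randomised sequences and is not an estimate of active versus sham. This follows from the article's own schedule and needs no assumption about effect size. The visit label used in the Abstract, the Design section and the secondary analysis conflicts with the open-label section, Table 1 and the interview section. By the arithmetic, the visit is week 20 from treatment start, 12 weeks after randomised treatment and 0 weeks after open-label tDCS.

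A reader might go on to say that the week-20 effect is diluted by a given proportion. The documents do not support that: any such figure needs an uptake rate and a response to open-label tDCS that the article does not give, plus an assumption that the active arms stay unchanged. Nor does the point reach the primary outcomes. EDE-Q change is measured to week 8 and completed sessions are counted within the 8 weeks, both before open-label treatment starts.

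**What to change.** 1. In the secondary analysis, limit effects described as active versus sham to weeks 4 and 8, and to week 8 only for the neurocognitive tests, AQoL-4D and CSIE-32.
2. Report week 20 by randomised arm, with open-label uptake shown for each arm. If a contrast is kept there, label it: active-first versus sham-first, each followed by optional open-label tDCS.
3. Replace the 20-weeks-post-treatment label in the Abstract, the Design section and the secondary analysis with: week 20 (12 weeks after the end of randomised treatment; end of the open-label phase).

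The cost is wording plus a tabulation of open-label uptake. No visit or measure changes. What is given up is a sham-controlled reading of week 20, which the design cannot support.

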#### Secondary outcomes

A range of secondary outcome measures will be administered to further determine rTMS and tDCS treatment effects on: (1) weight, (2) mood, (3) neurocognition (attention and cognitive flexibility, field dependence vs independence, response inhibition, perseveration), (4) psychological symptoms, (5) quality of life, (6) interpersonal relations, (7) experience of treatment (optional semi-structured interviews), (8) economic outcomes (health sector costs including rTMS and tDCS administration, medications, psychology sessions, length of stay, and number of hospital readmissions). See Table 1 for measures.

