AN patients in previous studies were either in-patients receiving pharmacotherapy and psychotherapy [7] or out-patients with or without ED treatment [20, 21]. In this study, all participants will start as inpatients who will be receiving intensive concomitant treatment, i.e., comprehensive in-patient program with individual medication and/or psychotherapy and group cognitive behavioural therapy (CBT). This study will therefore explore, for the first time, the potential for additional therapeutic benefits of brain stimulation combined with existing eating disorders interventions.

AN has one of the highest treatment costs of any psychiatric disorder, largely due to the high cost of recurrent hospitalisation for nutritional rehabilitation [35]. Our study will explore the potential for these treatment modalities to reduce the length of hospital stays and emergency readmissions. Health economic data for both treatment modalities will additionally have utility from a service perspective, given the disparity in resource requirements between the two treatments (TMS, tDCS) in terms of costs for patients and access to treatment for people living in remote and rural areas (i.e., for at-home tDCS).

AN has been associated with impaired quality of life and lower preference-based health state utility values [2, 42, 49]. Utility values are used to calculate quality adjusted life years (QALYs) and used as an outcome measure by health technology assessment agencies such as the Pharmaceutical Benefits Advisory Committee in Australia and The National Institute for Health and Care Excellence in the UK. Our analysis will investigate the potential for these treatments to improve the quality of life and health state utility values for people with AN. This data will be useful for input into future trials and model based economic evaluations of these treatments.

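### As worded, the cost-effectiveness analysis names only inpatient-stay and follow-up readmission costs, which conflicts with the protocol's own economic outcome and leaves out stimulation delivery

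*Protocol article*

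**What the plan says.** Under Outcome measures (Secondary outcomes), the protocol article defines the economic outcome as "health sector costs including rTMS and tDCS administration, medications, psychology sessions, length of stay, and number of hospital readmissions". Table 1 has an "Administration cost" row, sourced from hospital data and ticked at every time point from weeks 1–3 to week 20. Medications, psychology sessions, length of stay and readmissions have rows of their own.

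Under Analysis (Secondary outcomes), two economic analyses follow one another. The first is a model-based comparison: "Generalised linear models will be used to compare cost and quality of life/utility values (from AQoL-4D) between treatments arms over the 8 week" randomised period. It names no cost items. The second is a cost-effectiveness analysis that sets health outcomes against "economic outcomes (costs of duration of inpatient stay and readmissions during the follow up period) associated with both treatment modalities".

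The Discussion says the health economic data will be useful from a service perspective, "given the disparity in resource requirements between the two treatments". After week 8, "participants in all groups will have the option of receiving an additional 12 weeks of daily (1 session per day") of at-home active tDCS, until the end of week 20.

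**The concern.** The bracket in the cost-effectiveness sentence has no word such as 'including' to show that it is a selection. Read as written, it drops three of the five cost items in the protocol's own definition: administration, medications and psychology sessions. Administration is the item that differs by design, because trained staff deliver all rTMS sessions while participants give themselves tDCS. A comparison of the two modalities that leaves it out cannot answer the question the Discussion poses.

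The same sentence takes readmissions from the follow-up period, when any arm may be receiving active tDCS, and it states no horizon for the health outcomes set against those costs. The Discussion intends the economic results as input to future trials and model-based evaluations, so an incomplete cost total or an unstated horizon could be carried forward.

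**Working it through.** **Cost items side by side**

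| Item | Economic outcome (Outcome measures) | Table 1 | Cost-effectiveness sentence (Analysis) |
|---|---|---|---|
| rTMS/tDCS administration | yes | weeks 1–3 through week 20 | not named |
| Medications | yes | weeks 1–3, 8, 20 | not named |
| Psychology sessions | yes | week 20 | not named |
| Length of stay | yes | weeks 4, 8 | named |
| Readmissions | yes | week 20 | named, follow-up period |

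**Session counts.** The Design section gives "84 sessions of tDCS (active or sham) or 56 sessions of rTMS (active or sham) over an 8 week treatment period". The schedules under Interventions reproduce both figures:

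- tDCS: 2 × 7 days × 4 weeks + 1 × 7 days × 4 weeks = 56 + 28 = 84.
- rTMS: 2 × 5 days × 4 weeks + 2 × 2 days × 4 weeks = 40 + 16 = 56.
- Open-label tDCS: 1 × 7 days × 12 weeks = 84 further sessions at most, as many as the randomised tDCS course.

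**What a literal reading omits.** Let c be the cost of one rTMS session and t the cost of one tDCS session. For fully treated participants, the delivery cost missing from the rTMS minus tDCS difference is

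56c − 84t.

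It is zero when c/t = 84/56 = 1.5. If c is more than 1.5t, leaving it out makes rTMS look cheaper relative to tDCS than it is. If c is less than 1.5t, the reverse holds.

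**Range under assumed unit costs.** The document gives none, so these values only illustrate:

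- c = 200, t = 5: 56 × 200 − 84 × 5 = 11,200 − 420 = +10,780 currency units per participant.
- c = 100, t = 20: 5,600 − 1,680 = +3,920.
- c = 50, t = 40: 2,800 − 3,360 = −560.

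The sign therefore depends on the assumption. Each participant who takes up the open-label option can add up to 84t in any arm, including the rTMS arms. For t from 5 to 40 that is 420 to 3,360.

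**Horizon.** The generalised linear models are limited to the 8 randomised weeks. The cost-effectiveness sentence puts readmissions in follow-up and sets no period for health outcomes. Table 1 schedules AQoL-4D at baseline, week 8 and week 20, so either horizon can be matched to utility data, but the text does not say which is meant.

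**The case against.** The strongest reply is that the plan as a whole does not ignore delivery cost. Administration cost is part of the defined outcome and is scheduled for collection throughout. The sentence immediately before the disputed one compares cost between arms over 8 weeks with no limit on cost items, and that period ends before any open-label treatment. The bracket does not say 'only', and in a condensed article it may be shorthand for the hospital costs that the Discussion most wants to explore. All of this stands, except that the 8-week cost model does not define the inputs of the cost-effectiveness analysis, whose own wording still conflicts with three other places in the article.

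A reader might infer more than the document supports:

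- *That the rTMS–tDCS cost difference will be wrong.* The 8-week model can include delivery, the bracket may be shorthand, and without unit costs no error can be sized or signed.
- *That open-label sessions go uncosted for lack of data.* Table 1 ticks administration cost at weeks 10 to 18 and at week 20.
- *That bed-days after week 8, or psychology sessions within the first 8 weeks, cannot be recovered.* A tick shows when data are gathered, not the period they cover. Hospital records may carry dates.
- *That using follow-up data is an error in itself.* The open-label option is disclosed and offered to every group. A 20-week comparison by randomised arm is legitimate if its delivery is costed and it is labelled for what it is.
- *That 8 weeks must be the base case.* That would miss most of the readmissions the Discussion wants to examine. The choice is a trade-off.

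**Conclusion.** The point holds as an internal inconsistency with a practical consequence. The cost list given for the cost-effectiveness analysis disagrees with the economic outcome under Outcome measures, with Table 1 and with the rationale in the Discussion. If the analyst follows the bracket literally, the incremental cost between modalities omits 56c − 84t per fully treated participant, along with medication and psychology costs. This assumes full attendance and a constant cost per session, and the amount vanishes only at c = 1.5t. Its size and sign are unknown.

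The finding is confined to the cost-effectiveness sentence. It does not touch the 8-week cost model, and it concerns an exploratory secondary domain of a self-described pilot with 70 participants. It should still be corrected before analysis, because relative cost effectiveness is among the study's stated expected outcomes and the repair is simple.

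**What to change.** In Analysis (Secondary outcomes), replace the bracket in the cost-effectiveness sentence with the full list from Outcome measures: rTMS and tDCS administration, medications, psychology sessions, length of stay and readmissions. State one horizon and measure both costs and health outcomes over it.

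Where follow-up to week 20 is used, include the delivery cost of open-label tDCS in every arm, from the administration cost already scheduled in Table 1. Label the result as a comparison by randomised arm that includes optional open-label tDCS and is not sham-controlled after week 8.

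The cost is a wording change and a little more analysis work on data already scheduled for collection.

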#### Qualitative data

Since thematic saturation may be achieved in 12 interviews [36], our aim is to collect qualitative data for 10–20 participants from each treatment group. Audio-recorded interviews will be transcribed verbatim in accordance with standardised guidelines [60] and will be analysed using inductive approach qualitative methods with use of the framework of thematic analysis [11]. This will include coding and generation of themes from participants accounts of their experience of rTMS and tDCS treatment.

